### Intervention Arm

Our VC team includes a technical person (a trained vision technician) and a community health worker (a VC attendant). Although the vision technician is responsible for patient examination, the VC attendant assists the vision technician and carries out community engagement activities. In addition, each region has a VC coordinator to supervise all VCs in that region. The intervention will include door-to-door screening and awareness generation in 8-12 villages in the catchment area of the intervention VC. We will leave the villages adjacent to the VCs and instead approach a mix of near and distant villages within our catchment area. A list of surrounding villages (within 10 km) will be prepared by the VC coordinator and the VC attendant. The VC coordinator will meet each village leader to take permission for the door-to-door intervention survey to be carried out in the village. After having received the necessary permissions, a priority list of survey villages will be prepared to initiate the intervention.

The VC attendant will be trained to use the Peek acuity application [22] for measuring visual acuity and using the data collection software Taraka on Android platforms. They will also be trained to use the developed information, education, and communication (IEC) material. In the intervention villages, the VC attendant will go from door to door. During the screening, if any house is locked or family members are not available, the VC attendant will attempt to contact those missing at least three times. The VC attendant will explain the intervention and obtain verbal consent for participation in the survey. Household or family members who are unwilling or not interested to participate in the survey will also be recorded separately.

After obtaining verbal consent for the screening, the VC attendant will communicate regarding the need for eye care in general and share the IEC material. For each family member above 5 years of age, the visual acuity of each eye will be measured and recorded using the PEEK acuity application on a smartphone. Demographic data, ocular complaints, and information regarding any previous eye checkup will also be recorded in the Android application.

Any person with a visual acuity of <6/12 (cutoff) or other eye issues will be counseled and referred for a comprehensive examination to the VC. A referral slip will be provided to the patient when referred, mentioning the reason for referral. Referred patients’ records will be accessible to the vision technician (optometrist) through the software. Patients reporting to the VC for a comprehensive checkup and treatment, due to the door-to-door intervention, will be recorded using vision center management software (VCMS). Any patient requiring surgical treatment or further care will be referred to the respective secondary center. Free cataract services will be provided to patients unable to afford the same. Follow-up of referred patients will be performed by the coordinators in the field.

### Control Arm

The control arm VC will continue its routine awareness activities and health talk sessions in the community. The VC attendant will prepare a monthly activity plan and organize activities in the surrounding 8-10 villages. Persons with eye issues will be recorded and referred to the VC for further evaluation and treatment. Patients reporting to the VC will be registered in the VCMS. For surgical intervention or further care, patients will be referred to the respective secondary center. Follow-up of referred patients will be performed by the coordinators in the field.

A comparison of the activities of the community health workers in the two arms is summarized in Table 1. The activities will be the same in both the arms and will also be standardized in the same manner; only their mode and reach will be different.

**Table 1 table1:** Comparison of activities of community health workers in the two study arms.

Serial number	Activity	Intervention arm	Control arm
1	Meeting with key stakeholders	Yes	Yes
2	Health talk sessions in community Refer patients to VC	No	Yes
3	Awareness activity through IEC distribution	Yes (door-to-door)	Yes (cluster meeting in village during visits)
4	Permission for door-to-door survey intervention	Yes	No
5	Door-to-door screening Refer patients to VC	Yes	No

### Project Timelines

The study period will be 12 months, of which 2 months will be spent preparing the study intervention and obtaining approvals, 3 months will be needed for preintervention work (ie, training the team, field preparation, finalizing the data collection format, and IEC development), and 4 months for the intervention and data collection; after data collection, the remaining 3 months will be used for data analysis and writing.

### Data Collection, Management, and Analysis

#### Data Collection and Variables

We will collect both electronic and manual data for both study arms. In the intervention arm, field-level data (door-to-door surveys) will be captured through software, while field-level activity in the control arm will be manually recorded in the activity register. VC-level data will be extracted from the VCMS, which will contain data for both control and intervention VCs. In both arms, programmatic data will be collected, which will include data of the villages screened, door-to-door screening, walk-in OPD visits, those reporting after referrals from the field, and spectacles advised and their uptake, as well as referrals for cataract, specialty, and surgical follow-up (Figure 1 and Multimedia Appendix 1). Cost data will be collected for direct, indirect, and opportunity costs, such as rent, human resources, overheads, and community activities (Multimedia Appendix 2). We will also collect data for revenue from the OPD, spectacles, and surgeries done.

Most of the data for analysis will be directly extracted from the existing software at the VCs. The rest of the data pertaining to the cost will be entered, collected, and monitored as part of regular processes in the field. This will make the data collection process streamlined and integrated into the regular operations. Although the costs incurred in running any program may vary for different providers, we feel that the detailed checklists will help in disaggregating that data for use by different service providers.

#### Quality Assurance

There will be three sources of data in this research. The data from the door-to-door screening will be collected using a customized Android application, the data of patients visiting VCs will be captured through the VCMS, and the additional data pertaining to activities from the control VCs and the visits of various members of the staff will be collected in the registers.

Checks and balances have been built into the software to ensure completion of data collection. A comprehensive checklist has been prepared to standardize the manual data collection. Random visits will be made periodically to the field to monitor screening, awareness generation activities, and data collection. Data collected during the day will be uploaded to the cloud server at least once at the end of the day, and that would be available for review. Thus, the quality of data will be ensured by the clearly defined roles of the team members involved in the intervention, appropriate resource allocation, and regular meetings with the team members. A regular review process will be followed to maintain quality assurance of the collected data, and at least 10% of the collected data will be cross-checked/verified by field supervisors. Surgery-related data of the patients referred from VCs would be extracted from the electronic medical records of the secondary hospital. Data will be collated monthly as part of routine program monitoring and independently audited. The composition of the data-monitoring committee is provided as Multimedia Appendix 3.

No adverse events for the screener or the participants undergoing screening are anticipated, as services being provisioned are per standard hospital protocols and no experimental treatment is being given. Any complications in this scenario will be reported and dealt with per standard hospital policies.

#### Data Analysis

The collected data will further be tabulated and analyzed by each study arm: distance of the village, age, gender, eye issues, visual acuity, compliance with treatment (medicine, surgery, glasses), and revenue and expenditure of VCs. The difference from baseline in the number of walk-in patients, referrals, uptake of services, and costs involved in intervention will be analyzed. The Z test for proportions will be performed to compare the change in walk-in patients between the two arms. *P*<0.05 will be considered statistically significant. Subgroup analysis with respect to age and gender will also be carried out.

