## Methods

### Study Design and Process

This study is a randomized, parallel-group experimental study in which we selected four VCs, two each in the intervention and control arms (one each from a particular operational area).

Our organization has six secondary centers, of which four are located in the state of Uttar Pradesh, namely Meerut, Mathura, Saharanpur, and Kheri. These regions have a total of 23 VCs operating in rural and semiurban areas, together serving around 1 million people. Of these four secondary centers, two were selected (Vrindavan in Mathura District and Mohammadi in Kheri District) for this study based on feasibility and the demographic profile of their catchment population.

The Vrindavan region has eight VCs delivering eye care services in its semiurban areas, while the Mohammadi region has six VCs (five rural and one semiurban). Most of these VCs have been operational for over 3 years. However, data from the previous year indicated that 80% of the VCs are suboptimal in their performance. The VCs performing suboptimally were listed. From a total of 10 VCs (5 in each region, meeting the inclusion/exclusion criteria), 2 were randomly selected from each region using the RAND function in Microsoft Excel (ie, 1 each for the control and the intervention arm). The process is illustrated in detail in Figure 1.

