### Sample Size

The average OPD attendance at the intervention centers is 7 per day at present. We expect to achieve 14 after the intervention, failing which, the intervention will not be considered a success. Therefore, the primary objective of the statistical analysis would be to estimate the average attendance, postintervention, with extreme precision, which will lead us to assess whether we have been able to achieve the target (14 per day, on average). We set the confidence interval (CI) to ±1 for the postintervention sample mean (the narrowest-possible CI in this case). To check whether at least 20 per day on average has been achieved, we expect a sample mean of at least 21 (ie, the CI will be 20-22). The number 20 has been determined based on a feasibility study conducted to project VC sustainability. We assume that the probability of the CI is 95% and the daily OPD attendance has a Poisson distribution. Thus, we expect that the postintervention daily attendance will have a Poisson distribution with a mean of at least 21. This implies that the variance of the distribution will also equal 21 (or more), and we want to estimate the mean with a 95% CI of ±1. This requires a minimum sample size of 81 days.

We used the following formula to calculate the sample size:

Sample size = (1.96^2^/*d*^2^) × Variance of the distribution

where 1.96 is the 97.5 percentile point of the standard normal distribution and d is the length of the CI (on one side of the estimate). If d = 1 and variance = 21, we obtain sample size = 81. We set a target of 20 per day in the pre-CODIV-19 time, but due to the pandemic, we revised our desired target to 14 per day to consider the intervention a success. We persisted with the additional days in the sample size (instead of 58 days for a target of 14) to be able to estimate up to 14 per day OPD attendance with precision.

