#### Cost-Effectiveness Analysis

Cost-effectiveness analysis and incremental cost-effectiveness analysis will be performed, and the incremental cost for every additional beneficiary attending the VC will be calculated. To calculate the increase in the number of patients, the average number of patients visiting per day during the same months in the previous year will be subtracted from the average in the study period. A change in the control VCs, if any, will be further deducted from this before using this as the denominator for calculating cost-effectiveness.

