### Outcomes

The primary outcome for this study will be an increase in the number of walk-in patients at the VCs from baseline (7-8 walk-in patients to 14 per day after the intervention period of 4 months). The secondary outcomes will be uptake of spectacles and uptake of surgery among those advised. If the intervention proves effective in terms of the number of people visiting the VCs, cost-effectiveness will also be a secondary outcome.

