### Limitations

Although we randomly selected the VCs from our two operational regions, the fact that we operate only in North India can be one limitation of our study. We had planned this study before the COVID-19 pandemic, and even after reasonable delay due to the unrelenting nature of the pandemic, we plan to start this study during the ongoing pandemic. Due to this, the target for the number of patients visiting the VCs has reduced. Although the conditions may not be near normal during data collection, we do not anticipate any difference in the way in which the intervention and control VCs would be affected by the prevalent conditions. Due to the nature of the intervention, it is not possible to mask the personnel on ground, and this may bring in some short-term behavior change, which may not be sustained. Another limitation of our study would be the short duration of data collection following the intervention. To analyze the long-term impact of the intervention, another study will be planned subsequently in case the results of this study show a positive impact.

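### Vision centers were randomized in pairs within region, but the named walk-in comparison has no region or center term, so differing regional recovery from the pandemic could be read as an effect

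*Protocol article*

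**What the plan says.** Study Design and Process describes the allocation: from five eligible VCs per region, "2 were randomly selected from each region using the RAND function in Microsoft Excel (ie, 1 each for the control and the intervention arm". Region is therefore the randomization stratum, with one pair of VCs in each.

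Data Analysis uses baseline ("The difference from baseline in the number of walk-in patients, referrals, uptake of services, and costs involved in intervention will be analyzed") and names one test: "The Z test for proportions will be performed to compare the change in walk-in patients between the two arms", at the 0.05 level. Age and gender are given as subgroups. Region and VC appear nowhere in that section.

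Cost-Effectiveness Analysis subtracts the previous year's average for the same months and then states: "A change in the control VCs, if any, will be further deducted from this before using this as the denominator for calculating cost-effectiveness". It does not say whether the deduction is made by region, or whether it is absolute or proportional.

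On attendance levels, Sample Size gives only an average: "The average OPD attendance at the intervention centers is 7 per day at present". Outcomes states the aim as "7-8 walk-in patients to 14 per day after the intervention period of 4 months". On the pandemic, Limitations says "we do not anticipate any difference in the way in which the intervention and control VCs would be affected by the prevalent conditions" and does not discuss differences between regions.

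**The concern.** The design pairs VCs by region, so each region's control shows what would have happened there without the intervention. A two-arm test that adds up each arm over both regions does not use that match. Each arm's change is then a mix of two regional trends, weighted by baseline volume, and the weights can differ by arm.

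The article gives reasons to take this seriously without establishing it:

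- The Vrindavan VCs are semiurban, while five of the six Mohammadi VCs are rural.
- The 10 km catchments are about 70,000 and 130,000 in the Mathura pair, but 111,000 and 110,000 in the Kheri pair.
- Data are collected during the pandemic, so recovery is a leading rival explanation for any rise. The assumption that both arms are affected alike is most credible within a region.

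At stake are the error rate of the primary comparison and the denominator of the cost per additional visit.

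**Working it through.** **Inputs from the article.** One VC per arm per region; average 7 per day at the intervention VCs (7-8 in Outcomes); target 14; eligibility ceiling 10 per day; Poisson daily counts; 81 days. The 81 reproduces: 1.96² × 21 / 1² = 80.67, rounded up. It is used here only as the length of each period.

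**Assumptions.** VC-level baselines and regional recovery are not reported, so all values for them below are assumed. There is no intervention effect and no VC-to-VC variation in change, and tests are two-sided.

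**Formulas.** Let I1, C1 be the intervention and control baselines in region 1 and I2, C2 those in region 2.

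- Proportional recovery r1, r2: pooled ratio of change = [(I1·r1 + I2·r2)/(I1 + I2)] / [(C1·r1 + C2·r2)/(C1 + C2)]. Difference in change per VC = [(I1 − C1)(r1 − 1) + (I2 − C2)(r2 − 1)]/2.
- Additive recovery a1, a2: difference in change = [(a1 + a2) − (a1 + a2)]/2 = 0, whatever the baselines.

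**Worked case at the article's own level.** I/C baselines 7/8 and 8/7, recovery 1.2 and 1.6:

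- Intervention: (7×1.2 + 8×1.6)/2 = 10.6. Control: (8×1.2 + 7×1.6)/2 = 10.4.
- Both start at 7.5, so the false difference is 0.2 per day and the false ratio is 10.6/10.4 = 1.019. Both within-region ratios are exactly 1.

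**False-significance rates** (Poisson simulation, 100,000 runs). Pooled ratio means a two-proportion Z test on each arm's study-period share of visits. Stratified ratio means the inverse-variance combination of the two within-region log ratios of change.

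| I/C baselines, region 1; region 2 | Recovery | False difference per VC per day | Pooled ratio | Pooled difference | Stratified ratio |
|---|---|---|---|---|---|
| 7/8; 8/7 | ×1.2, ×1.6 | +0.2 | 6.5% | 7% | 5% |
| 7/8; 8/7 | ×1, ×2 | +0.5 | 14% | 18% | 5% |
| 8/6; 6/8 | ×1.2, ×1.6 | −0.4 | 11-12% | 14% | 5% |
| 9/5; 5/9 | ×1.2, ×1.6 | −0.8 | 32% | 42% | 5% |
| 5/9; 9/5 | ×1, ×2 | +2.0 | 94% | 99% | 5% |
| 7/7; 7/7 | ×1, ×2 | 0 | 5% | 5% | 5% |
| 5/9; 9/5 | ×1.5, ×1.5 | 0 | 5% | 5% | 5% |
| 9/5; 5/9 | +1.4, +4.2 | 0 | 5% | 5% | 24-25% |
| 9/5; 5/9 | +1, +6 | 0 | 5% | 5% | 56% |

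The sign follows whichever arm holds the larger VC in the faster-recovering region.

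**A separate effect on the absolute scale.** If the arm means differ, equal proportional recovery is enough. With 7 against 9 in both regions at ×1.5, the false difference is (7 − 9)×0.5 = −1.0 per day, significant in 52% of runs. The pooled ratio stays at 1.00.

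**Cost-effectiveness denominator.** (ΔI1 − ΔC1) + (ΔI2 − ΔC2) = (ΔI1 + ΔI2) − (ΔC1 + ΔC2). An absolute deduction therefore gives the same total whether it is made by region or overall. Matching by region changes the total only if the deduction is proportional.

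**The case against.** **Pooling is inferred.** The article says the test is between the two arms; it does not say that counts are summed over regions, and an article may leave stratification terms to a fuller document. That is fair. Still, the test it names has no stratum term, and region is absent from an analysis section that does list other factors. The point concerns a stated choice, although not an explicit statement that pooling will occur.

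**Two stronger readings are not supported.** A reader might infer that baseline is ignored. It is not: change from baseline is analyzed, and what is missing is its region-matched, center-level use. A reader might also infer that a single overall control change is deducted in the cost analysis. The text leaves that open.

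**Pairing already cancels additive trends.** This stands. Bias in the pooled ratio needs recovery that differs by region together with baseline ratios that differ by region. Unequal baselines alone do not produce it.

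**The large rates come from mirror-image baselines.** This stands too. 9/5 against 5/9 is an extreme case and the article reports no VC-level baselines. At 7 and 8 the distortion is small beside the planned rise of 14 − 7 = 7 per day.

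**The remedy is not neutral.** The ratio analysis is biased under additive recovery, and Outcomes states the target as an absolute daily rise. This must be disclosed. With baselines drawn at random between 4 and 10, the stratified ratio rejects 5% against 10% for the pooled ratio under proportional recovery, and 26% against 24% under additive recovery. So it gains in one case and is about equal in the other.

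**Two pairs are few.** The 5% in the last column depends on zero VC-to-VC variation in change. With real variation, Poisson standard errors are too small for every analysis shown.

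**Conclusion.** The point holds in limited form. Randomization was within region, the named comparison has no region or VC term, and the control deduction in the cost analysis is not matched to region.

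Under proportional recovery that differs by region, with baseline ratios that also differ, pooling by arm creates a false effect. At assumed VC baselines of 7 and 8 it is about 0.2 to 0.5 visits per day, with a false-positive rate of about 6% to 18%. Only strongly unequal VC baselines, which the documents do not report, make it larger. On the relative scale it vanishes if baselines or regional recoveries are equal; on the difference scale it vanishes if recovery is additive.

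A reader might infer that the trial's main conclusion is at serious risk. The documents do not support that: a true doubling would be detected with close to 100% power either way. The distortion matters most for a modest effect and for the cost per additional visit. Using the pairing is a near-free improvement and should be made.

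**What to change.** **Data Analysis.** Make the comparison within region from each VC's own baseline. Either fit a count model with VC, region × period and arm × period terms, the last being the effect, or combine the two within-region ratios of change. Report both regional results beside the combined one.

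**Scale.** Prespecify it, and show the absolute difference in change alongside. State that the ratio is biased if recovery is additive and the difference if it is proportional with unequal baselines.

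**Cost-Effectiveness Analysis.** Deduct each region's own control change from its intervention VC, and state whether the deduction is absolute or proportional.

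**Limitations.** State that two pairs limit inference and that Poisson standard errors ignore VC-to-VC variation in change.

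**Cost.** No new data: VC-level attendance for both arms is already in the vision center management software. The main price is that a relative primary analysis differs in scale from the absolute target in Outcomes, so the two must be reported together. One degree of freedom also goes to the region-specific trend.

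### The between-arm test of walk-in patients is a Z test for proportions with no proportion defined, on an outcome the protocol itself treats as a Poisson count; its most direct reading is invalid

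*Protocol article*

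**What the plan says.** The Outcomes section sets the endpoint: "The primary outcome for this study will be an increase in the number of walk-in patients at the VCs from baseline", with a move from 7-8 to 14 per day over the 4-month intervention. The Sample Size section gives the starting point, "The average OPD attendance at the intervention centers is 7 per day at present", and the distribution: "We assume that the probability of the CI is 95% and the daily OPD attendance has a Poisson distribution". The Cost-Effectiveness Analysis section takes the mean daily attendance in the study period, subtracts the mean for the same months a year earlier, and then deducts any change in the control centres.

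The Data Analysis section names one between-arm test and ties it to a 0.05 significance level: "The Z test for proportions will be performed to compare the change in walk-in patients between the two arms". Nowhere does the article say what the proportion is. The outcomes that are naturally proportions are the secondary ones: spectacle uptake and surgery uptake among those advised.

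Four vision centres (VCs) are used, two per arm, one per arm in each region.

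**The concern.** A two-sample Z test for proportions takes its standard error from p(1-p)/n, the variance of a number of successes out of n trials. A change in visits per day is a difference of two counts. It can be negative or larger than the baseline, and its variance comes from both counts. The named test therefore conflicts with the distribution assumed in the Sample Size section and with the net difference in the cost-effectiveness section.

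This is more than a detail left to a later document. The article positively names a test of the wrong type for its primary outcome, and an analysis plan that follows it inherits the problem. This test is the only named inference that uses the control arm. If the denominator is chosen at analysis, significance can depend on that choice. A finding that more people attend is also what brings in cost-effectiveness as an outcome and feeds the decision on scaling up.

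**Working it through.** **The plan's own figure.** n = 1.96² × variance / d². With variance 21 and d = 1, n = 3.8416 × 21 = 80.67, rounded up to 81, so "If d = 1 and variance = 21, we obtain sample size = 81" is reproduced. The 58 days quoted for the lower target match variance 15 (3.8416 × 15 = 57.6). This is a precision calculation for one Poisson mean. No between-arm test enters it, and it is not in dispute.

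**Inputs.** Baseline 7 per day and target 14 (Sample Size); two VCs per arm (Study Design and Process). Assumed: 81 days per VC in each period, so 2 × 81 = 162 VC-days per arm per period; independent Poisson counts; two-sided 0.05. Baseline visits per arm are 7 × 162 = 1,134.

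**1. Same data, different denominators.** Take 7 to 8.0 in the intervention arm (1,296 visits) and 7 to 7.5 in the control arm (1,215 visits). The pooled two-proportion Z is:

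| Proportion | Intervention | Control | Z | P |
|---|---|---|---|---|
| change/baseline | 162/1,134 = 0.143 | 81/1,134 = 0.071 | 5.50 | 4e-8 |
| change/post | 162/1,296 = 0.125 | 81/1,215 = 0.067 | 4.94 | 8e-7 |
| post/catchment (210,000 per arm assumed) | 0.00617 | 0.00579 | 1.62 | 0.10 |
| post/(pre+post) | 1,296/2,430 = 0.533 | 1,215/2,349 = 0.517 | 1.11 | 0.27 |

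For comparison, a Poisson difference-in-differences on the log rate gives ln(8.0/7.5) = 0.0645, with SE = √(1/1,134 + 1/1,134 + 1/1,296 + 1/1,215) = 0.0580. Then Z = 1.11 and P = 0.27. Only the last row of the table agrees with it.

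**2. Type I error of change/baseline.** Let both arms rise equally from 7 to λ, and let R = λ/7. Under Poisson counts the variance of the between-arm difference is about 2R²(1/(162λ) + 1/1,134). The Z test uses 2p(1-p)/1,134 with p = R - 1.

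| λ | True SE | SE used | Ratio | Approximate type I error | Simulated |
|---|---|---|---|---|---|
| 8 | 0.0657 | 0.0147 | 4.47 | P(\|Z\| > 1.96/4.47) = 66% | 66% |
| 10 | 0.0782 | 0.0208 | 3.76 | 60% | 60% |
| 13 | 0.0967 | 0.0147 | 6.58 | 77% | 77% |

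In the same simulations, post/(pre+post) gave 4.9-5.1%.

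**3. At the target.** Under change/baseline from 7, the intervention value is (14 - 7)/7 = 1.00 and an unchanged control arm gives 0. So p(1-p) = 0 in both arms, and the unpooled Z is undefined. Simulated at those means, the intervention value exceeds 1 in 50% of runs, the control value is negative in 50%, and at least one lies outside 0-1 in 75%.

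**4. Centre-level variation.** Paired by region there are two differences, so 2 - 1 = 1 degree of freedom. Within-region re-randomisation has 2 × 2 = 4 allocations, so the smallest two-sided P is 2/4 = 0.5. If the VC-level change varies with an assumed coefficient of variation of 0.05, 0.10 or 0.20, even the post/(pre+post) test has a simulated type I error of about 13%, 32% or 58%.

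**The case against.** The strongest reply is that a proportions test on these data can be legitimate. For independent Poisson counts, post/(pre+post) is a proper conditional binomial proportion, and comparing it between arms tests the change. It holds its size, gives the same answer as the Poisson model at the modest effect, and stays well defined at the planned effect (0.667 against 0.500, Z = 12.5). This stands. A reader might infer that no valid denominator exists and that any proportions test here is wrong; the documents do not support that. What the reply cannot show is that the plan means this version: nothing in the article points to it.

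A reader might also infer that the test simply breaks down at the planned effect. That needs the change/baseline reading, a baseline of exactly 7 and the unpooled variance. The Outcomes section gives 7-8, and from 8 the target gives (14 - 8)/8 = 0.75. The pooled Z can still be computed at 1.00 against 0 (47.6), though from a variance that does not describe the data.

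Finally, the stated success rule does not rest on this test: "We expect to achieve 14 after the intervention, failing which, the intervention will not be considered a success". It is judged on the postintervention mean and its CI. That also stands and limits the damage. But that rule makes no use of the control arm, so any claim that attendance rose because of the intervention falls back on the between-arm comparison.

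How region is adjusted for is detail that an article may leave to a fuller document, and is not held against it.

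**Conclusion.** The point holds in this form: the Data Analysis section names a proportions test for a count outcome, defines no proportion, and is at odds with the Sample Size and cost-effectiveness sections. Under its most direct reading, change/baseline, the test is invalid, with a type I error of about 60-77% when both arms rise equally to 8, 10 or 13 per day. An equal rise is a realistic case: the study runs during the pandemic, and the cost-effectiveness section allows for a change in the control centres. Across the readings tried on one data set, P runs from 4e-8 to 0.27.

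These sizes assume independent Poisson counts and 162 VC-days per arm per period. Different window lengths or extra-Poisson variation would change the figures. The conflict over the type of data depends on neither.

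**What to change.** Replace the Z-test sentence in Data Analysis with a count or rate comparison that matches the rest of the protocol. One option is an overdispersed Poisson or negative binomial model of visits per VC, with VC, period and arm × period terms. Leave out a region main effect: each VC lies in one region, so it is collinear with the VC effects. Handle region by pairing VCs within region or by a region × period term. Report the ratio of rate ratios and, as in the cost-effectiveness section, the net difference in patients per day, each with a 95% CI.

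The text should also say that:

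- VC-level inference has about 1 degree of freedom when paired by region and is very imprecise;
- a CI or P value that treats days as independent leaves out between-VC variation, so P<0.05 is not to be read as confirmatory. The count model does not cure this.

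Keep the Z test for true proportions, such as spectacle or surgery uptake among those advised.

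The cost is a rewritten passage and modest extra analysis on data already held in the centres' management software. It also means accepting openly that two centres per arm cannot support a firm significance claim.
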